## Abstract

**Background:**

In Canada alone, almost 3000 VLBW infants are born and treated annually with almost 1200 going onto death or survival with severe brain injury, chronic lung disorders, aggressive retinopathy of prematurity, late-onset sepsis, or significant necrotizing enterocolitis. Lactoferrin is an antimicrobial, antioxidant, anti-inflammatory iron-carrying, bifidogenic glycoprotein found in all vertebrates and in mammalian milk, leukocytes and exocrine secretions. Lactoferrin aids in creating an environment for growth of beneficial bacteria in the gut, thus reducing colonization with pathogenic bacteria. It is hypothesized that oral bovine lactoferrin (bLF), through its antimicrobial, antioxidant and anti-inflammatory properties, will reduce the rate of mortality or major morbidity in very low birth weight preterm infants.

**Method:**

Lactoferrin Infant Feeding Trial_Canada (LIFT_Canada) is a multi-centre, double-masked, randomized controlled trial with the aim to enroll 500 infants whose data will be combined with the data of the 1542 infants enrolled from Lactoferrin Infant Feeding Trial_Australia/New Zealand (LIFT_ANZ) in a pooled intention-to-treat analysis. Eligible infants will be randomized and allocated to one of two treatment groups: 1) a daily dose of 200 mg/kg bLF in breast/donor human milk or formula milk until 34 weeks corrected gestation or for a minimum of 2 weeks, whichever is longer, or until discharge home or transfer, if earlier; 2) no bLF with daily feeds. The primary outcome will be determined at 36 weeks corrected gestation for the presence of neonatal morbidity and at discharge for survival and treated retinopathy of prematurity. The duration of the trial is expected to be 36 months.

**Discussion:**

Currently, there continues to be no clear answer related to the benefit of bLF in reducing mortality or any or all of the significant neonatal morbidities in very low birth weight infants. LIFT_Canada is designed with the hope that the pooled results from Australia, New Zealand, and Canada may help to clarify the situation.

**Trial registration:**

Clinical Trials.Gov, Identifier: NCT03367013, Registered December 8, 2017.

## Background

Over 15 million infants are born preterm (< 37 weeks gestation worldwide [1]. In developed countries such as Canada, Australia and the United States, very low birth weight infants (VLBW < 1500 g) preterm infants account almost 1.5% of all births [2–4]. In Canada alone, almost 3000 VLBW infants are born and treated annually with almost 1200 going onto death or survival with severe brain injury, chronic lung disorders, aggressive retinopathy of prematurity (ROP), late-onset sepsis (LOS), or significant necrotizing enterocolitis (NEC) [2]. Each of these morbidities has been associated with a substantial risk of childhood impairments [5–7].

Lactoferrin is an antimicrobial, antioxidant, anti-inflammatory iron-carrying, bifidogenic glycoprotein found in all vertebrates and in mammalian milk, leukocytes and exocrine secretions [8, 9]. Lactoferrin has been shown to be effective against infection when tested in animals and in the laboratory [10–12]. The systemic effects of oral lactoferrin are generally thought to be indirect and probably are initiated by contact with intestinal epithelial cells and gut-associated lymphoid tissue (GALT) [13, 14]. Lactoferrin and other similar products in human milk create an environment for growth of beneficial bacteria in the gut, reducing colonization with pathogenic bacteria. However, most VLBW infants receive insufficient human lactoferrin from human breast milk in the first months of life, resulting in suboptimal protection [15]. Because human lactoferrin is expensive, bovine lactoferrin has been considered as an alternate supplement to improve this suboptimal protection, as it has at least 70% amino acid homology with human lactoferrin with the same N-terminal peptide [16]. With the properties outlined, lactoferrin has emerged as a potential new tool for the prevention of serious neonatal morbidities.

There have been 6 randomized controlled trials involving almost 1100 preterm infants that have evaluated oral bovine lactoferrin (bLF) in the most recent Cochrane review (2017) [17].

The review showed that lactoferrin supplementation to enteral feeds decreased late-onset sepsis (typical risk ratio (RR) 0.59, 95% confidence interval (CI) 0.40 to 0.87; typical risk difference (RD) -0.06, 95% CI − 0.10 to − 0.02; and NEC stage II or III (typical RR 0.40, 95% CI 0.18 to 0.86; typical RD -0.04, 95% CI − 0.06 to − 0.01. Lactoferrin supplementation did not have an effect on “all-cause mortality” (typical RR 0.65, 95% CI 0.37 to 1.11; typical RD -0.02, 95% CI − 0.05 to 0). Lactoferrin supplementation to enteral feeds with or without probiotics decreased late-onset sepsis involving bacterial and fungal organisms but not chronic lung disease or length of hospital stay. Investigators reported no adverse effects and did not evaluate long-term neurological outcomes and periventricular leukomalacia. However, because of the moderate to low quality of the evidence as per the GRADE criteria [18], the Cochrane review called for the results of at least the 6 additional ongoing trials including LIFT_Canada to provide data to enhance the quality of the evidence.

### Collaboration with LIFT_Australia/New Zealand (LIFT_ANZ)

The Canadian-funded component of LIFT (LIFT_Canada) will enroll 500 participants to add to the 1542 participants already enrolled in LIFT_ANZ. By combining over 2000 recruited infants, the combined LIFT will have > 80% power to detect a 19% reduction in death or serious morbidity from a control rate of 26 to 19.5% at 2-tailed *p* < 0.05, which is clinically important, plausible, and more conservative than earlier trial results.

If LIFT confirms a 19% reduction in the RR of its primary outcome, bLF will have a major impact, translating into thousands more intact survivors without major morbidity in Australia, New Zealand, Canada, Europe and worldwide each year. As> 90% of very preterm survivors at hospital discharge reach adulthood [19, 20], this represents more than 19,000 life-years gained in Canada alone each year, one of the largest gains in intact survival - in any specialty - since neonatal surfactant and antenatal steroids [21, 22]. In addition, by following the infants to 24 months corrected age (CA), information on neurodevelopmental outcomes which is currently lacking will also be provided as survival without major morbidity has been associated with an improved chance of a positive neurodevelopmental outcome by 2 years corrected age [23].

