### Rationale for continuing LIFT_Canada

Earlier in 2019, two large trials presented results, the Enteral Lactoferrin supplementation for very preterm infants (ELFIN trial) [24, 25] and Lactoferrin for Infant Feeding Trial_Australia New Zealand (LIFT_ANZ) [26].

In 2203 infants in the ELFIN Trial (2203 infants), lactoferrin was associated with a relative risk (risk ratio) for late onset sepsis of 0.95 (95% CI 0.86–1.04) [25]. This confidence interval did not reliably exclude a 14% reduction or a 4% increase in sepsis. In the 1417 infants in ELFIN who received formula for > 50% of days of enteral feeds, lactoferrin was associated with a relative risk for sepsis of 0.89 (95% CI 0.79–1.01). This did not reliably exclude a 21% reduction or 1% increase in sepsis in this subgroup. Overall, ELFIN did not rule out important potential benefits, particularly for infants who receive formula for over half of days of enteral feeds.

In 1542 infants in LIFT_ANZ, lactoferrin was associated with a relative risk for late onset sepsis of 0.82 (95% CI 0.63–1.07). LIFT_ ANZ did not rule out a 37% reduction or 7% increase in sepsis. (Presented at the 7th International Conference on Clinical Neonatology, Torino, Italy, May 2019).

When ELFIN is combined with LIFT_ANZ and all other trials, a total of 5011 infants, the overall effect of lactoferrin is to reduce the relative risk of late onset sepsis to 0.82 (95% 0.74–0.92; *P* = 0.0004), with moderate heterogeneity (I^2^ = 0.58) and asymmetric funnel plot, consistent with small study effects (personal communication, [name]).

Similarly, a meta-analysis of the effect of bLF on late onset sepsis in 1891 preterm infants who were not fed exclusively mother’s own milk in two RCTs of bLF supplementation [25, 27, 28], a relative risk of late onset sepsis to be reduced to 0.82 (95% 0.71–0.96; *P* = 0.01), with moderate heterogeneity (I^2^ = 0.64) and asymmetric funnel plot, consistent with small study effects, or true differences between trials in effectiveness or underlying patient risk [29].

This is consistent with a more moderate but clinically relevant average benefit in reducing sepsis with no evidence of harm and no clear increase in mortality, NEC, sepsis or other adverse outcomes. Consequently, a decision to continue enrollment has been supported by the Steering Committee for LIFT_Canada and LIFT_ANZ.

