### Statistical analysis

Analysis sets are defined as the following:
The intention-to-treat (ITT) population will comprise all randomized infantsThe Per Protocol population will comprise all randomized infants that receive at least one administration of their assigned treatment and who are not deemed ineligible on blinded clinical reviewA second Per Protocol population will comprise all randomized infants who received the minimum required administrations of 14 days of their assigned treatment and who are not deemed ineligible on blinded clinical review.The safety population will comprise all randomized infants who received at least one dose of the assigned treatment. Infants will be analysed according to the treatment they received for the purposes of the safety analysis.

An interim analysis of the primary composite endpoint and of survival to discharge using the Haybittle-Peto [28] approach in the first 250 infants enrolled in the study in Canada. The procedure involves evaluating the test statistic calculated under the null hypothesis against a boundary of 3 standard deviations (equivalent to χ^2^ = 9, with a *p*-value of 0.0027. This will have a negligible effect on the alpha level applicable at the final analysis.

A two sided alpha (significance level) of 5% will be applied to the analysis of the primary composite endpoint. There will be no adjustment for the interim analysis evaluated using the Haybittle-Peto boundary [30].

The key secondary endpoints for LIFT_Canada comprise the individual components of the primary composite (survival, brain injury, NEC, LOS, and ROP). *P*-values adjusted for the 5 comparisons performed for this set of endpoints will be derived using the Benjami-Hochberg procedure [31] with a family wise error rate of 5%. Results of other endpoints, subgroup, and sensitivity analyses will be interpreted in proper context and with due consideration of type 1 error.

The primary analysis in LIFT_Canada is a pooled analysis utilizing the individual data of infants recruited in Canada combined with the data of the infants recruited in the LIFT_ANZ trial. Safety analyses will be performed using the safety population. Non-safety analyses will be performed using the ITT population. Sensitivity analyses will be performed using the Per Protocol populations. In addition, information will be presented as Canadian data only and combined poled (Canada and ANZ) data.

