## Discussion

Currently, there continues to be no clear answer related to the benefit of bLF in reducing mortality or any or all of the significant neonatal morbidities in very low birth weight infants. Pooled data suggests benefit in some outcomes, in particular late onset sepsis. Benefit may be augmented in conjunction with current aspects of care such as use of human milk and probiotics in the vulnerable infants. It is hoped that the results of LIFT_Canada alone and pooled with LIFT_ANZ may help to clarify the situation.

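### The stated power of over 80% does not describe what 500 more infants can settle once 75.5% of the pool has been reported, and a 19% reduction does not reach it even unconditionally

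*Protocol article*

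**What the plan says.** Under Collaboration with LIFT_Australia/New Zealand, LIFT_Canada "will enroll 500 participants to add to the 1542 participants already enrolled in LIFT_ANZ". The next sentence gives the power: "By combining over 2000 recruited infants, the combined LIFT will have > 80% power" at a two-tailed 5% level, "to detect a 19% reduction in death or serious morbidity" and, in the same phrase, "from a control rate of 26 to 19.5" per cent.

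Under Rationale for continuing LIFT_Canada, the article says "Earlier in 2019, two large trials presented results". One of the two is LIFT_ANZ, for which it gives a late-onset sepsis relative risk of 0.82 (95% CI 0.63 to 1.07). After reviewing this and other evidence, the section ends: "Consequently, a decision to continue enrollment has been supported by the Steering Committee for LIFT_Canada and LIFT_ANZ".

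Statistical analysis makes the pooled individual-data analysis of Canada and ANZ the primary analysis, tested at two-sided 5%. It also promises a presentation of the Canadian data alone. The ANZ result on the primary composite appears nowhere in the article.

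**The concern.** A power figure stated for the whole pool treats every infant's outcome as still unknown. Here the article itself shows that about three quarters of the pool had been analysed and had informed the decision to go on. From that point, the probability of a significant pooled result is set largely by a test statistic that is already fixed, and only the 500 Canadian infants remain random. A reader who takes the stated power as the prospect of the continuing trial may be badly misled, in either direction.

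The sentence also fails on its own inputs. A fall from 26% to 19.5% is not a 19% reduction, and the two effect sizes have clearly different power. What is at stake is whether funders, ethics boards and parents know how much the remaining enrolment can resolve.

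**Working it through.** **Inputs.** Canada 500 and ANZ 1542, control risk 26%, effect sizes of a 19% relative reduction and 26% to 19.5%, two-sided 5% (Collaboration section). Allocation is 1:1 (Randomisation). The pool is 2042, or 1021 per arm. The ANZ share is t = 1542/2042 = 0.755.

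**Step 1. Check the stated effect.** (26 − 19.5)/26 = 0.25, a 25% reduction. A 19% reduction from 26% ends at 0.26 × 0.81 = 21.06%.

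**Step 2. Unconditional power.** With n = 1021 per arm and p̄ the mean of the two risks,

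power = Φ{[(p₁ − p₂) − 1.96·√(2p̄(1 − p̄)/n)] / √(p₁(1 − p₁)/n + p₂(1 − p₂)/n)}.

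- 26% to 21.06%: (0.0494 − 1.96 × 0.01877)/0.01874 = 0.67, power **74.9%**. Reaching 80% needs 1157 per arm, 2314 in total.
- 26% to 19.5%: (0.0650 − 1.96 × 0.01855)/0.01850 = 1.55, power **93.9%**. Reaching 80% needs 652 per arm.

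The claim of more than 80% is therefore true only as a loose inequality for the 25% reduction, and is not met for the 19% reduction. A one-sided test would give 83.8% for the latter, but the text says two-tailed. These figures ignore correlation between siblings; an assumed design effect of 1.1 lowers them to 70.9% and 91.7%.

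**Step 3. Conditional power given ANZ.** Let z be the ANZ composite test statistic (positive favours lactoferrin) and D the expected pooled statistic under the assumed effect. D = 0.0494/0.01874 = 2.64 for the 19% reduction and 0.0650/0.01850 = 3.51 for 26% to 19.5%. Then

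CP = Φ{[√t·z + (1 − t)·D − 1.96] / √(1 − t)}, with √t = 0.869, 1 − t = 0.245 and √(1 − t) = 0.495.

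Example at z = 1.0, 19% reduction: (0.869 + 0.645 − 1.960)/0.495 = −0.90, CP = 18%.

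| Assumed ANZ composite z | CP, 19% reduction | CP, 26% to 19.5% |
|---|---|---|
| 0 | 0.4% | 1% |
| 0.5 | 4% | 9% |
| 1.0 | 18% | 32% |
| 1.47 | 47% | 64% |
| 1.9 | 75% | 87% |

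The row at 1.47 borrows the sepsis result: −ln(0.82) / [(ln 1.07 − ln 0.63)/3.92] = 0.198/0.135 = 1.47. Sepsis is one component of the composite, so this row is an illustration only.

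**Step 4. What ANZ result would be needed?** Setting CP to 80% and solving gives z of about 1.99 (two-sided p about 0.047) for the 19% reduction and about 1.75 (p about 0.08) for 26% to 19.5%.

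**Step 5. If one assumes only that the ANZ composite was non-significant.** Averaging CP over |z| < 1.96 under each effect gives about **40%** for the 19% reduction and **62%** for 26% to 19.5%.

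**The case against.** **Design-stage power is conventionally unconditional.** The trial was registered in December 2017, before the 2019 presentation, so the pooled design and its power may predate the ANZ results. Keeping a sample size fixed in advance is defensible. This stands as a defence of the design. It does not cover an article written after the results, which uses them to justify continuing and still states the power in the future tense.

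**The size rests on a number that is not shown.** This stands. The article gives only the sepsis component for ANZ. The Discussion remark that "Currently, there continues to be no clear answer related to the benefit of bLF" concerns the evidence in general and says nothing definite about the ANZ composite. The conditional figures are a range under stated assumptions. The unconditional shortfall for a 19% reduction needs no such assumption.

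**The dependence is partly disclosed.** The rationale section is open about continuing after ANZ, and Canada-only results are already planned. What is missing is the consequence for power.

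**A stronger reading is tempting: that the 5% test is inflated because the ANZ report is an uncounted look.** Statistical analysis says "There will be no adjustment for the interim analysis evaluated using the Haybittle-Peto boundary", and that interim covers only the first 250 Canadian infants. Two unadjusted 5% tests at 75.5% and 100% of the information would have an overall error of 7.3%. That needs ANZ alone to count as a second confirmatory chance for this trial, and the article does not say so. A single pooled test completed regardless of ANZ keeps its 5%. Continuing only if the ANZ z exceeded 0, 0.5 or 1 would leave the upper-tail error at 2.5%, 2.5% and 2.4%, so it is not raised. A stricter final critical value of 2.04 is not called for either: it is unnecessary for a single test, and if ANZ had been a confirmatory test at 1.96, the overall error would still be 6.7%.

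**Conclusion.** The point holds for power. The stated figure of more than 80% does not describe the chance that the remaining 500 infants produce a significant pooled result. That chance reaches 80% only if the ANZ composite z was about 1.99 or more (19% reduction) or 1.75 or more (26% to 19.5%). Below those values it falls quickly, to 18% and 32% at z = 1.0. Independently of ANZ, the sentence joins two different effects, and the 19% reduction that it names has about 75% power.

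The results rest on 1021 per arm, a 26% control risk, the normal approximation, no allowance for sibling correlation, and the assumption that the sponsor holds the ANZ composite result. The true conditional power cannot be fixed from the article and could lie above or below 80%. The pooled analysis remains valid to run at its stated 5% level.

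**What to change.** 1. State the effect consistently, and give the unconditional power for each effect size that is kept: about 75% for 26% to 21.06% and about 94% for 26% to 19.5%, before any allowance for siblings.
2. Add the conditional power of the pooled test given the ANZ composite result that the sponsor holds, at each effect size, and say that 75.5% of the pool was known when the decision to continue was taken.
3. Label the already planned Canada-only estimate as the part independent of the known ANZ data.

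No change to the 5% level or the critical value is needed. The cost is wording and a probably less favourable stated power. It requires no additional infants.

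### The only power statement gives figures that cannot all hold: 26% to 19.5% is a 25% relative reduction, and a 19% reduction from 26% has about 75% power, not more than 80%

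*Protocol article*

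**What the plan says.** The power statement stands in the Background of the protocol article, under Collaboration with LIFT_Australia/New Zealand (LIFT_ANZ). LIFT_Canada "will enroll 500 participants to add to the 1542 participants already enrolled in LIFT_ANZ". The resulting claim for the pooled trial concerns "power to detect a 19% reduction in death or serious morbidity from a control rate of 26 to 19.5" (both rates in per cent). This power is put above 80%, for a two-tailed test at the 0.05 level. The next paragraph of that section uses the effect again: "If LIFT confirms a 19% reduction in the RR of its primary outcome". That wording makes the 19% a relative reduction, that is, a risk ratio (RR) of 0.81.

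No other section gives a control rate, a treated rate or a power figure for the composite. The abstract repeats only the numbers of infants. Randomisation gives 1:1 allocation, and Statistical analysis gives a two-sided 5% level without adjustment for the interim analysis.

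**The concern.** One sentence fixes the effect in two ways that disagree. The percentage says 19% and the pair of rates says 25%, which is too far apart for rounding. The stated power then belongs to one of the two effects and not to the other.

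The sentence matters because it is the only justification of the pooled sample size in the article, and the pooled analysis is the primary analysis. The 19% is also the effect that the trial is expected to confirm, and the projected public-health gain rests on it. A reader who takes 19% and more than 80% together assumes that such an effect would be missed less than 20% of the time. From a 26% control rate it would be missed about 25% of the time. The reader also cannot tell which effect the trial was sized for.

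**Working it through.** **Inputs, all from the protocol article**
- Infants: 500 + 1542 = 2042, so n = 1021 per arm at 1:1 (Collaboration with LIFT_ANZ; Randomisation).
- Two-sided 5%, z = 1.960 (Statistical analysis).
- Control rate 26%, treated rate 19.5%, reduction 19%, power above 80% (Collaboration with LIFT_ANZ).
- Infants are treated as independent. This is an assumption of the check; the article states no allowance for clustering.

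**Step 1. Do the rates give 19%?**
- 1 − 19.5/26 = 1 − 0.75 = 25% relative, or 6.5 points absolute.
- 26% × (1 − 0.19) = 21.06%.
- Keeping 19.5% and RR 0.81 gives a control rate of 19.5%/0.81 = 24.07%.
- Read as an absolute difference, 19 points would mean 26% to 7%, which conflicts with both 19.5% and the wording about the RR.

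**Step 2. Formula for power**

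For two proportions with difference d = p1 − p2 and mean p̄ = (p1 + p2)/2:

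SE0 = √[2p̄(1 − p̄)/n], SE1 = √{[p1(1 − p1) + p2(1 − p2)]/n}, power = Φ[(d − 1.960 × SE0)/SE1].

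**Step 3. The plan's own rates, 26% to 19.5%**

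d = 0.065, SE0 = 0.01855, SE1 = 0.01850. (0.065 − 0.03637)/0.01850 = 1.548, so power = 93.9%. The claim of more than 80% is true here, with a wide margin. For these rates 80% power needs only 1304 infants.

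**Step 4. The plan's own 19%, with each stated rate in turn**
- 26% to 21.06%: d = 0.0494, SE0 = 0.01877, SE1 = 0.01874. (0.0494 − 0.03680)/0.01874 = 0.672, so power = 74.9%.
- 24.07% to 19.5%: d = 0.04574, SE0 = 0.01827, SE1 = 0.01824. (0.04574 − 0.03581)/0.01824 = 0.544, so power = 70.7%.

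**Step 5. Does the choice of method matter?**

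For 26% to 21.06% the alternatives give:

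| Variant | Power |
|---|---|
| Unpooled variance | 75.0% |
| Wald test on the log risk ratio | 74.6% |
| Continuity correction | 73.2% |
| 2000 infants instead of 2042 | 74.1% |

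None reaches 80%. A one-sided 5% test would give 83.9%, but the article specifies a two-tailed test.

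**Step 6. What 80% would take**
- About 2314 infants for 26% to 21.06%, against 2042 planned.
- With 2042 infants and a 26% control rate, the smallest relative reduction with 80% power is about 20.2% (26% to 20.75%, power 80.1%).

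**Step 7. Correlation among multiples**

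The primary model allows for correlation between siblings. The article gives no figure for it. Assuming design effects of 1.05 to 1.2, the 74.9% falls to about 73% to 67%, and the 93.9% to about 93% to 89%.

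**The case against.** The best defence is that the sentence gives two explicit rates and that the power claim is true for them, at about 94%. On that view 19% is a slip and nothing else is wrong. Part of this stands: a reader might infer that the power figure is impossible in itself, and the article does not support that. The fault lies in the combination. But the defence requires 19% to be wrong in both places where it appears. It would also mean that the 1542 infants already enrolled exceed the 1304 needed for 80% power at those rates, which sits awkwardly with adding 500 infants to reach the stated power.

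A reader might also infer that a 19% reduction could never have 80% power with 2042 infants. That goes too far. With a control rate of about 28.6% or more, RR 0.81 does reach 80%. The article states no such rate for the composite, so this does not rescue the sentence.

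A third tempting inference concerns the chance of success given LIFT_ANZ, which had already presented results. The article reports only its late-onset sepsis result and no result for the composite. A conditional power for the primary endpoint therefore cannot be derived from it, and leaving one out is not an error.

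Finally, the practical harm can be overstated. The article reads other trials' inconclusive results through confidence intervals, and the significance level, analysis population and model are fixed independently of this sentence. That limits the consequence but does not make the figures agree.

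**Conclusion.** The power statement is wrong as written. The stated rates imply a 25% relative reduction, not 19%, and with either stated rate a 19% reduction does not have the stated power: about 75% from a 26% control rate, and about 71% to a 19.5% treated rate. The stated power holds only for 26% to 19.5% (about 94%).

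The arithmetic in step 1 needs no assumption. The power figures assume 1021 infants per arm, complete outcome data and independent infants; correlation among multiples would probably lower them. The repeated 19%, once tied to the RR, suggests that 19.5% is the misprint, but does not prove it. Correcting the treated rate alone would not suffice, because power would still be about 75%. None of this shows that enrolment must change.

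**What to change.** In Collaboration with LIFT_Australia/New Zealand (LIFT_ANZ), the sponsor should establish which effect the pooled trial was sized for, make the treated rate, relative reduction and power agree, and use that one effect in both paragraphs. If the control rate of 26% is kept, wording such as this would do:

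*With 2042 infants and a two-sided 5% level, power is about 75% for a 19% relative reduction (26% to 21.1%) and about 94% for a 25% relative reduction (26% to 19.5%); 80% power corresponds to a relative reduction of about 20.2% (26% to 20.75%). These figures ignore correlation among multiples.*

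The second decimal in 20.75% should stay, because exactly 20.8% gives 79.3%. The cost is a change of wording. Enrolment and the analysis stay as they are, but the power quoted for a 19% reduction becomes less favourable.
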